### Definitions of the primary variables and measuring methods

The main study variable is the proportion of subjects who attain the LDL-C levels set as targets by the Guidelines for Management of Dyslipidaemias and CVR, across a follow-up period of 24 months. The plasma values taken as cardiovascular prevention targets are: a) LDL-C <100 mg/dl for patients without established cardiovascular disease or diabetes mellitus; and, b) LDL-C <70 mg/dl for patients with diabetes mellitus or established cardiovascular disease.

The secondary variables are as follows: adherence to lifestyle guidelines and adherence to drug treatment, as seen from self-reported adherence (adapted Haynes-Sackett test), validated questionnaire (Morisky-Green test) and Likert scale with 5 response options;variation in plasma lipid profile levels at 2, 6, 12, 18 and 24 months (total cholesterol, LDL-C, HDL-C and triglycerides);variation in cardiovascular risk level across follow-up, with assessment to be performed using the SCORE (low CVR countries) and REGICOR tables;appearance of cardiovascular events in the observation period, i.e., ischaemic heart disease, atherothrombotic cerebrovascular disease, heart failure and peripheral arterial disease;physical activity, i.e., determination of the degree of aerobic physical exercise performed (active, partially active or inactive);determination of the frequency of food consumption;smoking habit, with a smoker being defined as anyone who answers affirmatively to the question, “Do you smoke?”;anthropometric measures, i.e., weight, height, body mass index (BMI), and waist circumference;systolic and diastolic blood pressure (two measurements), with the result being the mean of the two results;health problems (WONCA ICPC-2 classification) and drug use;use of hypolipidaemic drug treatment (type of drug and dose);socio-demographic data, including age, sex, marital status, educational level and social class;beliefs and expectations about preventive recommendations: fulfilment of initial expectations in terms of improvement obtained and related drawbacks (questions with 5 Likert-type response options ranging from 1 “much more than expected” to 5 “much less than expected”); and,degree of satisfaction with the combined strategy according to a satisfaction questionnaire (Likert scale with 5 response options ranging from 1 “very dissatisfied” to 5 “very satisfied”).

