### Selection of subjects

Eight health centres in the Albacete, Zaragoza and Vigo Health Areas have been chosen for strategic reasons. To prevent contamination bias, the control group participants will belong to areas different to those of the experimental groups. Accordingly, participants will be randomised on a health-area basis, with subjects then being consecutively selected.

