### Subject follow-up

Subjects will be monitored for a period of two years.

Selection will be made at primary care outpatient facilities, inviting patients who meet the inclusion criteria to participate in the study. Once they have given their consent, such patients will then be given an appointment for an initial visit and analysis.

During the initial visit, patients will be randomised to one of the two groups. Data will be collected from all participants covering medical history (socio-demographic variables, personal and family background, lifestyle habits), physical examination (anthropometric parameters, blood pressure), analysis (lipid profile, glucose) and calculation of cardiovascular risk. The routine standard recommendations, pharmacological and non-pharmacological, will be made for their treatment. An appointment will be made for the next visit.

Participants included in the intervention group will be given printed matter describing the disease and its management, along with treatment-compliance check cards, and they will be informed about the frequency and content of the mobile-telephone text messages that they will receive. Disease-management reminders will be dispatched every 15 days and reminders about attendance at pending appointments or missed appointments will be sent according to the follow-up dates.

With respect to follow-up, after the initial visit, 5 more will be made: these will take place at 2, 6, 12, 18, and 24 months. At each of these visits, anthropometric parameters (weight, BMI and waist circumference), blood pressure figures, lipid profile (total cholesterol, LDL-C, HDL-C and triglycerides), glucose and clinical history data will be recorded, and cardiovascular risk will be calculated. Data evaluating compliance with or adherence to treatment guidelines will be obtained for both groups of patients. Data on satisfaction will solely be recorded during the final visit, and then only for subjects in the intervention group.

Any of the following circumstances will be grounds for termination of the study in the case of any given participant: completion of the observation period (2 years); violation of the protocol; intercurrent disease that renders continuation of the intervention impossible; and withdrawal from the study/withdrawal of consent.

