### Statistical analysis

We will compare the variables of interest and the stratification and potentially confounding variables at baseline in both groups. The homogeneity of the two groups will be ascertained in terms of the baseline values of the study variables (Student’s t and chi-squared test, depending on the nature of the variables).

The subjects in the two groups will be classified into different LDL-C and total cholesterol reduction levels, and an initial crude analysis will be performed to assess the following parameters together with their respective 95% confidence intervals (CIs): absolute benefit increase (ABI); relative benefit increase (RBI); and number needed to treat (NNT).

Incidence of the outcome variables will be described and compared (proportion of subjects with appropriate control of lipid parameters and proportion of those who were guideline compliers) in both groups for each follow-up period (tests of comparison of proportions: Chi-squared test). Comparison of variations in lipid profiles in each group across the study will be made using the Student’s T-test or its non-parametric alternative (Mann–Whitney U test); and changes in the parameters in each group will be analysed using the T-test for repeated measures.

The possible existence of confounding factors or interaction of other variables in the relationship between the proposed intervention and the outcome variables will be assessed with the aid of logistic regression models (dependent variables: control of lipid parameters and therapeutic adherence). For continuous variables, assessment will be made using multiple linear regression.

Analysis will be conducted on an intention-to-treat basis, with all randomised patients being included in the analysis of effectiveness in accordance with their randomised group, regardless of the intervention received. In addition, a protocol analysis will also be performed for the main variables.

All analyses will be performed using the SPSS v20.0. computer software programme.

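### The primary LDL-C outcome uses two thresholds set by baseline diabetes or cardiovascular disease, but the stated comparison of proportions is not stratified by that target group and no adjustment for it is committed to

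*Protocol article*

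**What the plan says.** All references are to the protocol article.

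- **Outcome.** Definitions of the primary variables and measuring methods: "The main study variable is the proportion of subjects who attain the LDL-C levels set as targets". Two targets follow. Someone with neither diabetes nor established cardiovascular disease must fall below 100 mg/dl. The stricter one is "b) LDL-C <70 mg/dl for patients with diabetes mellitus or established cardiovascular disease".
- **Test.** Statistical analysis compares the proportion with appropriate lipid control "in both groups for each follow-up period (tests of comparison of proportions: Chi-squared test". No stratum enters this test. Absolute benefit increase (ABI), relative benefit increase and number needed to treat (NNT) are introduced as part of an initial crude analysis.
- **Stratification.** The same section says "We will compare the variables of interest and the stratification and potentially confounding variables at baseline in both groups". This is a baseline comparison, and the variables are not named.
- **Adjustment.** Confounding or interaction, if present, "will be assessed with the aid of logistic regression models (dependent variables: control of lipid parameters and therapeutic adherence". Target group is not fixed as a covariate.
- **Allocation.** Selection of subjects says "participants will be randomised on a health-area basis, with subjects then being consecutively selected" and draws control patients from different areas than intervention patients. Subject follow-up says "During the initial visit, patients will be randomised to one of the two groups". Study location and subjects lists eight centres in three health areas.

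**The concern.** Target group is not an ordinary prognostic factor here. It decides which cut-off a patient must pass, so two patients with the same LDL-C of, say, 85 mg/dl are scored differently. The pooled proportion is a weighted average of two attainment rates, with weights equal to each arm's share of patients held to each target.

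Two things follow. If attainment differs between the target groups, an analysis that ignores them carries avoidable variance. And if the arms differ in mix, the pooled difference moves without any difference in lipid control within either group. Whether the second is chance or bias depends on how patients are allocated, and the article describes that in two ways.

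**Working it through.** The plan gives no figure on this point to reproduce: neither the share of patients with the lower target nor attainment by target group.

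**Inputs from the article (Sample size):** control attainment 55%, intervention 75%, 155 evaluable and 179 enrolled per arm.

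**Assumptions:** share *s* with the <70 target = 30% (10% as an alternative); attainment gap *g* between target groups = 20, 30 or 40 points; no treatment effect unless stated.

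**1. Precision, patient-level randomisation.** Fraction of outcome variance explained by target group = s(1 - s)g² / [p(1 - p)], with p = 0.55, so the denominator is 0.2475.

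- s = 0.30, g = 0.20: 0.21 x 0.04 / 0.2475 = 3.4%
- s = 0.30, g = 0.30: 0.21 x 0.09 / 0.2475 = 7.6%
- s = 0.30, g = 0.40: 0.21 x 0.16 / 0.2475 = 13.6%
- s = 0.10, g = 0.30: 0.09 x 0.09 / 0.2475 = 3.3%

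The gap enters squared, so its sign does not matter here.

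**2. Validity, patient-level randomisation.** With no effect, every patient has the same marginal success probability in either arm, so the crude test is valid. A simulation (40,000 trials, 155 per arm, s = 0.30) gave type I error of 4.7% for g = 0.20 and 4.6% for g = 0.40. The chance difference in share has SD = sqrt(2 x 0.30 x 0.70 / 179) = 4.8 points (5.2 points at 155 per arm).

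**3. Shift when the arms differ in mix.** Shift = (difference in share) x g. Example with g = 0.30: attainment is 64% in the <100 group and 34% in the <70 group, which averages to 0.70 x 64 + 0.30 x 34 = 55%. With shares of 25% and 35%, the arms show 64 - 0.25 x 30 = 56.5% and 64 - 0.35 x 30 = 53.5%. The crude difference is 3 points. Within each target group it is 0, so the Mantel-Haenszel difference is 0.

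| Difference in share | g = 20 | g = 30 | g = 40 |
|---|---|---|---|
| 10 points | 2 | 3 | 4 |
| 20 points | 4 | 6 | 8 |

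(Shift in percentage points.) Against the planned 20-point effect, 3 points is 3/20 = 15%. NNT would move from 1/0.20 = 5.0 to 1/0.23 = 4.3 or 1/0.17 = 5.9, depending on direction.

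**4. When step 3 is bias.** Under patient-level randomisation, differences in mix are chance and the test already allows for them. With three health areas, one arm holds one area and the other two, so any difference between areas in diabetes or cardiovascular prevalence passes into the arms and does not shrink as more patients are enrolled.

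**The case against.** **A planned adjustment exists.** The chi-squared test is not the only analysis: a logistic model on lipid control is planned, and its covariate list could sit in a fuller document. This stands in part, and the absence of a list is not the complaint. What the article does state is an unstratified test and a model that looks for possible confounding. A factor that defines the outcome should not depend on such a search.

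**The endpoint is legitimate.** Scoring each patient against his or her own guideline target is sound. This stands; nothing here questions the two thresholds.

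**The loss is modest.** At 155 per arm, power for 55% v 75% is Φ[(0.20 - 1.96 x sqrt(2 x 0.65 x 0.35/155)) / sqrt((0.55 x 0.45 + 0.75 x 0.25)/155)] = Φ(1.77) = 96%, so losing a few per cent of precision would not sink the trial. This stands.

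**A stronger reading to avoid.** A reader might infer that the crude test has a seriously inflated false-positive rate. With a 20-point difference in share and a 30-point gap, rejection under no effect is about 18% at 155 per arm. The documents do not support this as a general statement. Under patient-level randomisation that imbalance is 20/4.8, about 4 SD, and the test keeps its nominal 5%. Under area allocation it is possible, but nothing in the article says how far the areas differ.

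**Sign and share are unknown.** A reader might also infer that more <70 patients must lower an arm's attainment. The Background cites targets met in about 32% of patients with dyslipidaemia, but about 53% without adequate control in a coronary study, which leaves about 47% controlled. Those studies' targets are not given, so neither direction is established. The exclusion of significant chronic organic disease could also make the share well below 30%.

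**Conclusion.** The point holds in limited form. Target group is part of the outcome definition, and the stated comparison ignores it without a firm commitment to adjust.

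- If patients are randomised individually, the crude test is valid. The cost is precision only: roughly 3-14% of outcome variance for a 30% share and 20-40 point gap, about 3% for a 10% share and 30-point gap.
- If allocation is by health area, the crude difference can also be biased by share difference times gap, for example 3 points for 10 and 30 points. The article gives no basis for saying how large the share difference would be.

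All sizes rest on assumed shares and gaps. The change is worth making because it helps under either reading of allocation, but it is a modest improvement and not a rescue of the design.

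**What to change.** In Statistical analysis, make the primary comparison a Mantel-Haenszel risk difference with a Cochran-Mantel-Haenszel test, stratified by baseline target group (<100 v <70 mg/dl). Alternatively, fix target group as a covariate in the logistic model already planned; because that model yields an odds ratio, ABI would then come from predicted probabilities averaged over the target groups. Take ABI and NNT for target attainment from the stratified estimate, and report attainment by arm within each target group beside the pooled proportion.

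The cost is wording and a standard analysis. Target group follows from the medical history recorded at the initial visit, the LDL-C targets do not change, and there is no material downside.

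This removes only the part of any area-level imbalance that comes from target mix. Other area-level confounding and clustering remain and must be handled separately, starting by reconciling Selection of subjects with Subject follow-up on the unit of allocation.

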### Statistical analysis

We will compare the variables of interest and the stratification and potentially confounding variables at baseline in both groups. The homogeneity of the two groups will be ascertained in terms of the baseline values of the study variables (Student’s t and chi-squared test, depending on the nature of the variables).

The subjects in the two groups will be classified into different LDL-C and total cholesterol reduction levels, and an initial crude analysis will be performed to assess the following parameters together with their respective 95% confidence intervals (CIs): absolute benefit increase (ABI); relative benefit increase (RBI); and number needed to treat (NNT).

Incidence of the outcome variables will be described and compared (proportion of subjects with appropriate control of lipid parameters and proportion of those who were guideline compliers) in both groups for each follow-up period (tests of comparison of proportions: Chi-squared test). Comparison of variations in lipid profiles in each group across the study will be made using the Student’s T-test or its non-parametric alternative (Mann–Whitney U test); and changes in the parameters in each group will be analysed using the T-test for repeated measures.

The possible existence of confounding factors or interaction of other variables in the relationship between the proposed intervention and the outcome variables will be assessed with the aid of logistic regression models (dependent variables: control of lipid parameters and therapeutic adherence). For continuous variables, assessment will be made using multiple linear regression.

Analysis will be conducted on an intention-to-treat basis, with all randomised patients being included in the analysis of effectiveness in accordance with their randomised group, regardless of the intervention received. In addition, a protocol analysis will also be performed for the main variables.

All analyses will be performed using the SPSS v20.0. computer software programme.

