### Sample size

The sample size needed for analysis will be calculated using a two-sided test, based a clinically relevant difference of 20% in the proportion of subjects who attain the lipid control targets, i.e., 55% in the control group, according to data furnished by previous studies (Kotseva et al. [8, 11]; Bueno et al. [18]), and 75% in the group undergoing the proposed intervention. Assuming a statistical power of 90% and an α error of 5%, the estimated sample size would then be 155 subjects in each group (total of 310 subjects). Assuming an expected proportion of losses of 15%, the final size of each group would be 179 subjects (an overall total of 358).

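### The protocol gives two units of randomisation; if health areas are allocated, the individual-level sample size and patient-level tests do not match the design

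*Protocol article*

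**What the plan says.** All references are to the Protocol article.

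- **Unit, first statement.** Selection of subjects says that, to avoid contamination, control patients come from areas other than those of the intervention patients, and that "participants will be randomised on a health-area basis, with subjects then being consecutively selected".
- **Unit, second statement.** Subject follow-up says that patients are randomised to one of the two groups at the initial visit.
- **Available units.** Study location and subjects gives three health areas containing eight health centres.
- **Sample size.** "The sample size needed for analysis will be calculated using a two-sided test", with "55% in the control group, according to data furnished by previous studies" and "75% in the group undergoing the proposed intervention", power 90% and α 5%; "the estimated sample size would then be 155 subjects in each group (total of 310 subjects"). Then: "Assuming an expected proportion of losses of 15%, the final size of each group would be 179 subjects". No ICC, design effect or number of clusters appears.
- **Analysis.** Outcome proportions are compared "in both groups for each follow-up period (tests of comparison of proportions: Chi-squared test"). Lipid changes use Student's t or Mann-Whitney tests. Logistic and linear regression are used to look for confounding and interaction. No area or centre term is named.

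**The concern.** Placing the arms in different areas is cluster allocation. Patients in one area or centre share doctors, prescribing habits and laboratories, so their outcomes are likely to be correlated. A patient-level chi-squared test ignores this. Its standard error is too small, its p-value is too low, and the intervals for absolute benefit increase (ABI), relative benefit increase (RBI) and number needed to treat (NNT) are too narrow. A difference between regions could then be reported as an effect of the intervention, and the Discussion foresees a guideline recommendation from a positive result.

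This is not a detail left to an unseen analysis plan. The article itself names the sample-size basis and the tests, and they fit only one of its two descriptions of allocation.

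**Working it through.** **1. The plan's own figure under independence.** Inputs from Sample size: 0.55 v 0.75, two-sided α 0.05, power 0.90.

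n = [1.96 × √(2 × 0.65 × 0.35) + 1.2816 × √(0.55 × 0.45 + 0.75 × 0.25)]² / 0.20² = 117.4, so 118 per group; 128 with continuity correction.

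The stated 155 is not reproduced. At 155 per group these inputs give about 96% power, and 155 matches 95% power with continuity correction. The 179 is 155 × 1.15 = 178.25, rounded up. How 155 arose is a separate point. What matters here is that the calculation treats patients as independent and carries an unexplained surplus of 155/118 = 1.31 (or 155/128 = 1.21).

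**2. Assumptions for clustering.** The documents give no ICC, so I take 0.005, 0.01, 0.02 and 0.05, with 155 evaluable patients per arm.

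- Design effect: DE = 1 + (m − 1) × ICC, where m is the cluster size.
- True type I error of the unadjusted test: 2 × [1 − Φ(1.96/√DE)].
- Power of a cluster-level test: noncentral t with noncentrality 0.20/√(0.435 × DE/155), where 0.435 = 0.55 × 0.45 + 0.75 × 0.25.

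**3. Areas allocated (three areas, 1 v 2).** One arm is a single area of 155; the other is two areas of 77.5. DE is averaged over the arms: 1 + ((154 + 76.5)/2) × ICC. The area-level test has 1 df and a critical value of 12.71.

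| ICC | Average DE | Type I error of chi-squared | Power, 1 df |
|---|---|---|---|
| 0.005 | 1.58 | 12% | 19% |
| 0.01 | 2.15 | 18% | 16% |
| 0.02 | 3.31 | 28% | 13% |
| 0.05 | 6.76 | 45% | 9% |

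A beta-binomial simulation (40,000 runs) gave type I errors of 18%, 28% and 46% at ICC 0.01, 0.02 and 0.05.

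**4. Centres randomised (not stated anywhere; shown for comparison).** Eight equal centres, 4 v 4, m = 310/8 = 38.75, 6 df. The normal approximation is Φ(noncentrality − 1.96), with unpooled variance.

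| ICC | DE | Type I error of chi-squared | Power, 6 df | Power, normal approx. |
|---|---|---|---|---|
| 0.005 | 1.19 | 7% | 82% | 93% |
| 0.01 | 1.38 | 9% | 76% | 90% |
| 0.02 | 1.76 | 14% | 66% | 81% |
| 0.05 | 2.89 | 25% | 46% | 60% |

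**5. What the surplus would cover.** Setting DE = 1.31 gives a centre-level ICC of (1.31 − 1)/37.75, about 0.008; DE = 1.21 gives about 0.006. Both hold only under the normal approximation.

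**6. Patients randomised individually.** Allocation adds no design effect, and the patient-level tests use the right unit.

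**The case against.** The strongest reply is that the protocol need not be a cluster trial at all. Subject follow-up randomises patients at a visit, the Design section describes a randomised parallel-group trial without mentioning clusters, and the Discussion relies on chance to balance patient characteristics. On that reading the sample-size formula and the tests use the right unit. This stands, and it is why the point is conditional. It does not remove the point, because individual randomisation cannot keep the arms in different areas, and the protocol gives a deliberate reason for keeping them apart.

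Second, 155 per arm exceeds the 118 to 128 that the inputs need, so some clustering could be absorbed. That is true for power at a very small centre-level ICC by the normal approximation. But the protocol does not present the surplus as a clustering allowance, and it gives no protection against type I error, which exceeds 5% for any positive ICC.

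Third, part of the low power comes from the few degrees of freedom and not from correlation. With ICC = 0 the 6-df test already has only 88% power and the 1-df test 23%. This is correct. It is a consequence of having so few units to allocate.

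Fourth, the ICC is assumed, so the size is a range and not a single result. The direction does not depend on the value chosen, provided that it is positive.

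**Conclusion.** The protocol is wrong as written, because it states two incompatible units of randomisation and its sample size and tests suit only one of them. If health areas are allocated, the unadjusted chi-squared test has a type I error of about 12% to 45% for an assumed ICC of 0.005 to 0.05, and a valid area-level test has under 20% power. With one arm a single area, the area and intervention effects are inseparable whatever the model or the number of patients.

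A reader might infer more than this, in three ways. One is that the trial is certainly cluster-randomised, so that its 90% power and 5% error certainly fail; Subject follow-up does not allow that certainty. Another is that the eight-centre figures describe the plan; no section allocates centres, makes them equal in size or splits them 4 v 4, so those figures are only an illustration. The third is that a model with centre as the cluster would repair area allocation; it would not, because centres are nested within the allocated areas.

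**What to change.** Reconcile Selection of subjects with Subject follow-up and state one unit of randomisation. Then, according to which applies:

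- **Patients randomised individually.** Delete the statements on area-basis randomisation and on keeping the arms in different areas. Stratify randomisation by centre and adjust for centre in Statistical analysis.
- **Centres randomised.** Replace the patient-level tests with a cluster-level comparison, or with a mixed or GEE model that has centre as the cluster and a small-sample correction. Report cluster-adjusted confidence intervals for ABI, RBI and NNT. In Sample size, state the ICC range, the design effect and the power that 358 patients give.
- **Whole areas allocated.** Withdraw the 90% power and 5% error statements, and say plainly that area and intervention effects cannot be separated.

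The cost is revised text and, in the two cluster cases, a less favourable statement of power. Individual randomisation brings back some of the contamination risk that separating the areas was meant to avoid. For area allocation, rewording makes the limitation visible but does not remove it; that would take more randomised units or true individual randomisation.

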## Discussion

Finding a type of action that could yield a higher success rate in the compliance and control of subjects with hypercholesterolaemia is fundamental when it comes to optimising available resources and improving the prevention and treatment of cardiovascular disease. This is why we feel that the most effective strategy will have to include activities targeted at enhancing knowledge about dyslipidaemia, reminding patients about guidelines and facilitating a higher patient participation rate. Similarly, we propose an action that is targeted, not only at pharmacological adherence, but also at the remaining recommendations for improving control of hypercholesterolaemia.

The results of the study will provide extremely useful information about the effectiveness of the proposed strategy of improving compliance in the prevention and management of cardiovascular disease based on increased control of lipid profile plasma levels. Should this intervention prove effective, a recommendation could then be issued on the application of the combined strategy to subjects with hypercholesterolaemia. Since it is a simple and relatively inexpensive intervention, it could be included as a recommendation in the respective clinical practice guidelines.

Selection biases will be reduced by using a randomisation procedure because it is not the researcher who allocates the intervention, and so any factor that might influence participation would affect both groups to the same degree. Likewise, confounding bias will be reduced by the effect of random chance, as a result of which any determinants that might influence the final result will tend to be shared between the intervention and control groups.

There is the possibility that the sample may not be representative of all eligible subjects, owing to differences between the persons who agree and those who do not agree to participate, posing a problem of external validity if the non-response rate proves to be high. For instance, persons who agree to participate in the study may possibly be more predisposed to follow guidelines than are the remaining candidates.

There could be a bias in data-collection due to the effect of regression towards the mean, applicable to analytical results. There is also the possibility of a risk of differential losses in follow-up between the groups compared, due to the duration of the study.

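### The stated lipid comparisons ignore baseline, and within-group paired tests are added that cannot show an effect of the intervention

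*Protocol article*

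**What the plan says.** Four statements in the protocol article, Statistical analysis, bear on this point.

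- Between arms, continuous lipids: "Comparison of variations in lipid profiles in each group across the study will be made using the Student’s T-test or its non-parametric alternative", the alternative being the Mann-Whitney U test. No baseline covariate is mentioned.
- Within arms: "changes in the parameters in each group will be analysed using the T-test for repeated measures".
- Binary outcomes: the proportions with lipid control are compared at each follow-up period by chi-squared test. Absolute and relative benefit increase and NNT come from an analysis that the section itself calls crude.
- Baseline: "The homogeneity of the two groups will be ascertained in terms of the baseline values of the study variables", by t and chi-squared tests.

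Regression appears after these, to assess possible confounding or interaction. Logistic models are named for lipid control and adherence, and then "For continuous variables, assessment will be made using multiple linear regression".

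Under Definitions of the primary variables, "The main study variable is the proportion of subjects who attain the LDL-C levels set as targets", with a limit of 70 mg/dl for patients with diabetes or established cardiovascular disease and 100 mg/dl for the rest. The lipid changes are secondary: "variation in plasma lipid profile levels at 2, 6, 12, 18 and 24 months". Under Subject follow-up, lipids and medical history are recorded at the initial visit, after eligibility and consent, and both arms then receive routine drug and lifestyle recommendations. The Discussion says "There could be a bias in data-collection due to the effect of regression towards the mean", and no analytic remedy is given.

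**The concern.** The trial asks whether the combined strategy does better than routine GP care. Only a contrast between arms answers that. A paired test within one arm asks whether lipids changed at all in patients diagnosed with hypercholesterolaemia who have just been given treatment advice. A fall is to be expected in both arms even if the added strategy does nothing. A significant result in one arm and not in the other is easily misread as a difference between arms.

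The between-arm lipid test does address the question, but it subtracts the baseline with a fixed slope of 1, where regression would estimate the slope. That loses precision when baseline and follow-up are imperfectly correlated.

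The same applies in milder form to the primary variable. Whether a patient reaches target depends on baseline LDL-C and on which of the two limits applies. Both are known at the initial visit, and the chi-squared test uses neither. Baseline significance tests do not help: under proper randomisation they test a hypothesis known to be true, and they say little about which covariates matter for the outcome.

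**Working it through.** **Plan's own figure.** The protocol gives no SD, correlation or power for the lipid-change analysis, so there is nothing to reproduce. The 155 per group under Sample size is for the binary primary variable. It is used below only as the number analysed per arm. (It does not reproduce at the stated 90% power: the usual formula for 55% v 75% gives 118 per group, or 128 with continuity correction. That is a separate matter, and this point does not rest on it.)

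**Precision of the lipid comparison.** Assume individual randomisation, equal SD σ at baseline and follow-up, and correlation r between them. The variance per subject is:

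- change score: 2σ²(1−r)
- follow-up value alone: σ²
- ANCOVA on follow-up adjusted for baseline: σ²(1−r²)

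The ratio of ANCOVA to change score is (1−r²)/[2(1−r)] = (1+r)/2. The change score is worse than ignoring baseline altogether when 2(1−r) > 1, that is, when r < 0.5.

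The documents do not give r, so a range is shown. Power is for 155 per arm, two-sided 5%, and an assumed true difference of 0.32 SD. The last column is the number per arm for 90% power at that difference.

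| r (assumed) | ANCOVA / change variance | Power, change score | Power, ANCOVA | n per arm, change v ANCOVA |
|---|---|---|---|---|
| 0.3 | 0.65 | 66% | 84% | 288 v 187 |
| 0.5 | 0.75 | 80% | 90% | 206 v 154 |
| 0.7 | 0.85 | 95% | 98% | 124 v 105 |
| 0.8 | 0.90 | 99.4% | 99.7% | 83 v 74 |

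Check at r = 0.5: the change-score SD is σ, the standard error is σ√(2/155) = 0.1136σ, and 0.32/0.1136 = 2.82. Then 2.82 − 1.96 = 0.86, which gives 80% power.

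**What the paired test responds to.** A simulation with no intervention effect and 155 per arm selected patients on total cholesterol of at least 250 mg/dl. It assumed a population mean of 210, an SD of 40 and single-measurement reliability of 0.6 to 0.9; none of these is in the protocol.

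- Baseline measured afresh after selection, the order described under Subject follow-up: mean change about 0; the paired test rejects in 4% to 5% of runs.
- Qualifying value reused as baseline: mean fall of 24 to 6 mg/dl as reliability goes from 0.6 to 0.9; the paired test rejects in 99% to 100% of runs.
- Between-arm change-score t-test: rejects in about 5% of runs in both cases.

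Selection-driven regression to the mean therefore matters for the within-group tests only if the qualifying value serves as baseline, or to the extent that errors in two tests close in time are shared. It does not bias the between-arm test under individual randomisation. Routine treatment and time trend were not simulated, but they act on both arms after baseline, and a paired test would attribute any such change to the arm as a whole.

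**Primary variable.** No size is given for the gain from adjusting target attainment, because the protocol does not give the distribution of baseline LDL-C or the share of patients under each limit.

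**The case against.** A reader might infer that the plan would present regression to the mean as benefit, and might attach a fall in mg/dl to each arm. The documents do not support this. No section says that a within-group fall will be read as an effect of the intervention. The measures of effectiveness contrast the two groups, and the Discussion openly names regression to the mean as a risk. Baseline lipids are taken at a visit after eligibility and consent, so most selection-driven regression should precede baseline. A mg/dl figure would apply only if the qualifying value were reused.

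Three further objections have weight.

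- The lipid-change analysis is secondary, and the gain is modest when r is high: 15% of variance at r = 0.7 and 10% at 0.8. This stands and limits the importance of the point.
- Regression is planned and could include baseline, and a journal article may leave the covariate list to the SAP. This stands in part: unnamed covariates are no fault here, and nothing says that they will be chosen after seeing the data. But the section does fix the role of each method. The stated comparisons are unadjusted, and regression is there to look for confounding or interaction.
- An unadjusted chi-squared test is valid for a binary outcome under individual randomisation, and baseline tests leave the effect estimate unchanged. Both are true. The criticism is of lost precision and uninformative p-values.

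Finally, Selection of subjects describes randomisation by health area, whereas Subject follow-up describes randomisation of patients at the initial visit. If allocation is by area, the arms may differ systematically at baseline. Change score and ANCOVA then estimate different things, and ANCOVA is not automatically unbiased. This also stands: adjustment is no cure for that design.

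**Conclusion.** The point holds as one of precision and interpretation. The within-group paired tests cannot separate the intervention from routine treatment, time trend or residual regression to the mean, so their p-values do not bear on the trial's question. The unadjusted change-score comparison is inefficient. Under individual randomisation and equal SDs, baseline adjustment cuts its variance by 35% at r = 0.3 and by 10% at r = 0.8. Where r is below 0.5, the change score is less precise than the follow-up value alone.

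The between-arm lipid test and the chi-squared test on the primary variable are not shown to be biased under individual randomisation. The range for r and the 0.32 SD difference are assumptions. The change is worth making because it is cheap; the validity of the main comparison does not depend on it. Confounding and clustering under allocation by health area are a separate issue.

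**What to change.** In the protocol article's Statistical analysis section, or in the SAP that implements it:

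1. Make the lipid analysis a between-arm ANCOVA on follow-up values adjusted for the baseline of the same lipid, or a mixed model over the 2, 6, 12, 18 and 24 month visits with the same adjustment. Report the adjusted difference with its 95% CI.
2. Analyse LDL-C target attainment by logistic regression with baseline LDL-C and target category (<70 v <100 mg/dl) fixed in advance. Report a standardised risk difference, from which the absolute benefit increase and NNT follow.
3. Label within-group changes as descriptive and give them without p-values.
4. Replace the baseline significance tests with a descriptive baseline table.
5. State that the baseline lipid is the value from the initial visit and not the qualifying value.

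The cost is wording only: lipids and the medical history that sets the target are already recorded at the initial visit. How centre or area enters these models must follow the allocation actually used, so the two descriptions of allocation have to be reconciled first.
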